### Sample size calculation

The study is powered based on the primary neuropsychological measures attention and executive function, determined with the EpiTrack Junior. We plan to study a continuous response variable from a late withdrawal (control) versus an early withdrawal (experimental) group with one control per experimental subject. For the sample size calculation, we used the reference values given in the Introduction and first validation of EpiTrack Junior [20], which presents reference values of healthy children and children with epilepsy. The mean (SD) EpiTrack Junior score in healthy children was 32.6 (2.40). In children with epilepsy the mean (SD) score was 29.5 (4.70). For sample size calculations, we calculated the sample size using the SD of the epilepsy patients. Based on numbers of patients operated on per year in the participating medical centers and excluding patients with incompletely resected lesions, multifocal MRI abnormalities, an epileptic EEG postoperatively and use of a maximum of three AEDs at time of surgery (the numbers derived from the previous retrospective study [16]), we estimated to expect to include at least 90 patients per year. By including at least 150 patients in the trial, with 75 patients per arm, we will be able to detect a true difference in the mean response of 2.16 points in EpiTrack Junior score (which corresponds to a difference of 0.46 SD) with a 2-sided alpha = 0.05 and power (1-beta) = 0.8. This difference is considered clinically relevant, as for the EpiTrack a 0.5 SD difference, can reflect a shift towards a milder impaired group of epilepsy patients [20]. One interim analysis according to O’Brien Fleming is planned after half of the planned number of patients has reached their endpoints. For reasons of possible dropout, we will aim to include 180 patients.

### Ethical approval

The multicenter trial will start in the University Medical Center Utrecht, the Netherlands, in November 2015. Ethical permission has been obtained from the ethical committee of the University Medical Center Utrecht, which is the leading ethical committee. Eight sites: University Hospitals of Lyon (HCL), France; University Hospital Strasbourg, France; Epilepsy Center Freiburg, Epilepsy Center Kork, University Hospital Heidelberg, Germany; Great Ormond Street Hospital for Children NHS Foundation Trust, London, and Young Epilepsy, Lingfield, United Kingdom; Western General Hospital Edinburgh, Scotland; Hôpitaux Universitaire de Genève, Switzerland, will join the trial shortly thereafter. Other centers, that have adequate experience with pediatric epilepsy surgery, are welcome to participate.

### Safety monitoring

To minimize the risk for the participants in the proposed trial, we will exclude patients with those characteristics that have previously been shown to predict unfavorable outcome [16]. In our retrospective cohort we simulated the prospective randomized trial on 478 patients who would be eligible based on their exact inclusion and exclusion criteria. In this group, the interval to start of AED reduction was not associated with seizure recurrences during or after AED withdrawal (*p* = 0.155, HR 0.94; CI 0.86–1.02 per 3 months), nor with eventual seizure freedom (*p* = 0.551, HR 0.96; CI 0.85–1.09) or seizure and AED freedom (*p* = 0.516, HR 1.01 CI 0.97–1.06, Cox regression analysis). Based on these analyses, we expect an overall comparable percentage of seizure recurrences in both treatments arms, similar to the number or recurrences encountered in everyday clinical practice when starting tapering of AEDs.

We appointed a Data Safety Monitoring Board (DSMB) that will analyze our data to warrant safety and to monitor inclusion rates and assess inclusion feasibility. At 24 months a blinded interim-analysis will be performed by the DSMB to investigate superiority of one of the treatment arms with regard to the primary outcome measure. If the difference in attention between groups is more than 1 SD (age appropriate average reaction time), the DSMB may advise to prematurely stop the trial, if early withdrawal shows to be superior, the remaining patients in the late withdrawal group who still await start of AED reduction are allowed to withdraw medication from that time on. A test result with a 2-sided *p* < 0.0054 will be declared significant.

With regard to safety; due to the design of the trial, an interim safety analysis comparing both treatment arms at one moment is not possible. This is because we expect in both arms relapse risks to increase particularly once AED withdrawal is started. Thus, in the early withdrawal group recurrences probably occur sooner than in the late withdrawal group, although the total risk of relapse at the end of follow-up is not expected to differ between groups. This implies that at interim time points, when inherently more patients are under AED reduction (at increased risk of relapse) in the early arm, a fair comparison of relapse between both groups is not feasible. To deal with this, we will assess safety in each arm separately. The study intervention will be considered safe when seizure recurrences occur in less than 40 % of both treatment arms. This percentage is chosen based on the general seizure freedom rate after childhood epilepsy surgery of 41 to 93 % [1, 2]. Based on previous identification of risk factors for seizure recurrences, we expect recurrence rates in the patients included in the trial to be < 30 %, due to exclusion of patients with identified risk factors [1, 16, 22, 23]. We do not expect, however, the seizure status to be better than in normal clinical practice. Because of the expected cognitive benefit due to a longer AED-free period, a 40 % rate of seizure relapse will still be accepted. The DSMB statistician will analyze the number of patients with seizure recurrences every 3 months during trial duration, in order to allow early awareness of unexpected high numbers of recurrences, exceeding the 40 % limit. In this sequential testing safety model (Fig. 2), a 1-sided *p* value < 0.05 will be considered significant for the safety monitoring [24, 25].

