The trial’s primary outcome measure at 1 year after surgery is cognitive functioning, in terms of attention and executive functioning, which will be assessed using the EpiTrack Junior [20]. As secondary cognitive outcome measure, intelligence will be tested with the Wechsler Preschool and Primary Scales, the Wechsler Intelligence Scale for children, or the Wechsler Adult Intelligence scale, depending on the children’s age and capabilities; scores derived are Verbal (VIQ), Performal (PIQ) and Full-scale IQ, perceptual organization or reasoning and information processing speed index scores. We will measure baseline neuropsychological status maximum 3 months before surgery (t1), and thereafter at 12 months (±2 months) (t2) and 24 months (±2 months) (t3) postoperatively. Patients and/or parents will at all neuropsychological test points complete three types of questionnaires to assess the secondary outcome measures: the Child Behavior Checklist (CBCL) and the the Hague Side Effects Scale (HASES) [21] will be completed by the parents, and the Pediatric Quality of Life Inventory^TM^ (PedsQL™) will be completed by both parents and patients. This design will allow us to assess whether cognitive performance is better in the early AED-withdrawal group, with patients being AED-free at 1 year following surgery, compared to the group that is still on full medication at the first postoperative time point. It will also enable the study of differences at a later follow-up time point, when both groups have completely discontinued medication (t3) (Fig. 1). Seizure outcome will be assessed at the moment of randomization, as seizure freedom is an inclusion criterion, at 24 months after surgery, and at 20 months following start of AED withdrawal. This design allows us to assess differences in seizure outcome at equal AED-free intervals for both groups, and at 2 years after surgery irrespective of length of AED freedom.

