### Data Safety Monitoring Board

The DMSC analyses the unblinded data on a permanent basis and formulates recommendations for the Steering Committee on the continuation of the trial. The Data Monitoring Committee may also offer unsolicited recommendations. Members of the Data Monitoring Committee are: [name]. [name], child neurologist, epileptologist, UMCG; [name] [name], statistician, UMCU; [name]. [name], neurologist, UMCU.

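### The interim superiority rule is stated inconsistently: it names the primary outcome but stops on 1 SD of reaction time, and it does not say how that criterion combines with p < 0.0054

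*Protocol article*

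**What the plan says.** All references are to the Protocol article.

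- **Outcome.** Study design: "The trial’s primary outcome measure at 1 year after surgery is cognitive functioning, in terms of attention and executive functioning", assessed with the EpiTrack Junior. Safety monitoring says the interim analysis examines superiority on this primary outcome.
- **First criterion.** Safety monitoring, on when the board may advise stopping early: "If the difference in attention between groups is more than 1 SD (age appropriate average reaction time".
- **Second criterion.** The same paragraph ends by declaring a two-sided p below 0.0054 significant. Nothing links the two criteria.
- **Trigger.** Sample size calculation: one O'Brien-Fleming interim analysis "is planned after half of the planned number of patients has reached their endpoints". Safety monitoring: "At 24 months a blinded interim-analysis will be performed by the DSMB", with no origin given for the 24 months.
- **Blinding.** Safety monitoring calls the look blinded. The Data Safety Monitoring Board section says "The DMSC analyses the unblinded data on a permanent basis".
- **Design figures.** Sample size calculation: "we will be able to detect a true difference in the mean response of 2.16 points in EpiTrack Junior score", with 75 patients per arm; "In children with epilepsy the mean (SD) score was 29.5 (4.70"); "The mean (SD) EpiTrack Junior score in healthy children was 32.6 (2.40").

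**The concern.** This rule can end the trial early, so the board needs to know which variable is tested, against which threshold, and when. As written, the test is on EpiTrack Junior but the advice to stop hangs on reaction time, which appears nowhere else as an outcome. The board would have to guess which SD is meant: a reaction-time SD (none is given), the epilepsy SD of EpiTrack, or a healthy norm, which the reference to an age-appropriate average could suggest.

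The guess matters because the article's two EpiTrack SDs put the 1 SD rule on opposite sides of the p < 0.0054 rule. Depending on the SD chosen, and on whether the criteria are joined by 'and' or 'or', the board could be held to a threshold that is almost never reached or to one that spends more type I error than planned. The double wording on trigger and blinding adds to the uncertainty.

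**Working it through.** **Inputs.** SD 4.70 (epilepsy) and 2.40 (healthy), difference 2.16 points, 75 per arm, two-sided alpha 0.05, at least 90 inclusions per year, 150 evaluable and 180 to be included (Sample size calculation); interim p < 0.0054 (Safety monitoring); final test at two-sided 0.05 (Outcome parameters, which uses 95% confidence intervals). Assumptions: the scores in the trial have SD 4.70; accrual is uniform; the 1-year endpoint falls 8 to 12 months after inclusion, because inclusion lies between surgery and month 4.

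**The plan's own figures.** 2.16/4.70 = 0.46 SD. With 75 per arm, power is 0.804 (normal) or 0.798 (t), so the stated 80% is reproduced. An exact two-look O'Brien-Fleming design at half information gives an interim p of 0.0052 and a final p of 0.0480. The stated 0.0054 (z = 2.782) is therefore essentially the O'Brien-Fleming level for half information.

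**The two criteria at 75 children (37.5 per arm).** In SD units, SE = √(2/37.5) = 0.231. For a threshold b, z = b/SE, and the chance of crossing at the design effect is P(Z > (b − 0.46)/0.231).

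| Rule | Threshold b | z | two-sided p | chance of crossing |
|---|---|---|---|---|
| p < 0.0054 | 2.782 × 0.231 = 0.64 SD (3.02 points) | 2.78 | 0.0054 | 21% |
| 1 SD = 4.70 points | 1.00 SD | 4.33 | 0.000015 | 1% |
| 1 SD = 2.40 points | 2.40/4.70 = 0.51 SD | 2.21 | 0.027 | 41% |

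With 90 children (half of 180), SE = √(2/45) = 0.211. The p rule then needs 0.59 SD (2.76 points) and is crossed with chance 27%. The 1 SD rules give p = 0.000002 (4.70 points, chance 0.5%) and p = 0.015 (2.40 points, chance 40%). The pattern is the same.

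A reaction-time SD cannot be placed in this table because the article gives none.

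**Type I error.** From the bivariate normal with correlation √0.5 and a final test at 0.05, overall alpha is:

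- 0.052 with p < 0.0054 at the interim;
- 0.066 (75 children) or 0.058 (90 children) with the 2.40-point rule used alone.

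**Trigger.** Month at which half is reached = (planned/2)/90 × 12 + lag. Endpoints at month 24 = (24 − lag)/12 × 90.

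| Planned | Lag (months) | Half reached at month | Share with endpoint at month 24 |
|---|---|---|---|
| 180 | 12 | 24 | 90/180 = 50% |
| 180 | 8 | 20 | 120/180 = 67% |
| 150 | 12 | 22 | 90/150 = 60% |
| 150 | 8 | 18 | 120/150 = 80% |

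Within these assumptions the two triggers meet only for 180 children and a 12-month lag. The O'Brien-Fleming level is 0.010 at 60% information, 0.014 at 67% and 0.024 at 80%. If accrual were half the plan (45 per year, an assumption; the Discussion warns that recruitment may be difficult), month 24 would give 45 to 60 endpoints, or 25% to 40%, where the level is at most about 0.002.

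**The case against.** The strongest reply is that the article does contain a workable rule: one O'Brien-Fleming look at half of the endpoints, on the primary outcome, at two-sided p < 0.0054. That stands. A reader might infer that the board has no valid boundary at all; the recalculated 0.0052 shows otherwise.

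It can also be said that a p-value and an effect size are different kinds of criterion. The board only may advise stopping, so 1 SD could be a relevance condition on top of significance. With 1 SD = 4.70 points the rules are nested: every difference above 1 SD also passes p < 0.0054. That is a fair reading, but the article does not state it. Differences from 0.64 to 1 SD still pass one rule and fail the other, and with 2.40 points the order reverses.

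A reader might also set 21% against 1% and report a roughly 20-fold difference in the chance of stopping. That holds only if 1 SD is 4.70 points; with 2.40 points the ratio is about 2 in the other direction.

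On timing, 24 months can be read as the projected date of the half-endpoint look, and with more than half the information 0.0054 is merely conservative. Even at 30% information, overall alpha with a final test at 0.05 is only about 0.053. This is an ambiguity, not a proven contradiction. On blinding, the comparison can be run on coded arms, and the unblinded access may describe the three-monthly safety monitoring. The article does not say so, but the conflict may be one of wording only.

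Finally, a reader might object that a stop would precede the late arm's 32-month seizure assessment. At the planned accrual that is true under either trigger, so it is no argument for one over the other.

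**Conclusion.** The point holds as an inconsistency in a stated decision rule. The measure is contradictory within one paragraph (primary outcome against reaction time), and the relation between 1 SD and p < 0.0054 is undefined. At 75 children, the chance of crossing at the design effect is 21% under the p rule, and 1% or 41% under the 1 SD rule, depending on which of the article's two SDs is meant. Only the 2.40-point reading, used as a sufficient criterion, would raise type I error materially, to about 0.066 (0.058 at 90 children). These sizes assume an SD of 4.70 in the trial, equal arms, normal scores and a final test at 0.05.

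The two triggers and the two descriptions of blinding are wording to reconcile. They do not invalidate the interim analysis. The point should be fixed; it does not undermine the design.

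**What to change.** State one rule, identically, in Sample size calculation, Safety monitoring and Data Safety Monitoring Board:

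1. The board tests the EpiTrack Junior difference at the 1-year assessment once, when half of the planned patients have that endpoint. Say whether this is half of 150 (75) or half of 180 (90).
2. The boundary is the O'Brien-Fleming value for the information actually reached, about 0.0054 at half.
3. Remove the reference to reaction time. If an effect-size condition is kept, express it in EpiTrack points with a named SD, and require it in addition to the p boundary, never as an alternative.
4. Give 24 months only as the projected date of the look, with its origin.
5. Say whether the board sees coded or identified arms at this look, and how that relates to its ongoing unblinded access.

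The cost is wording in the protocol and the board's charter. Sample size and patients are not affected, and Trial status says that no patients have yet been included.

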## Background

For children with refractory epilepsy, epilepsy surgery is a successful and widely accepted therapeutic option with postoperative seizure freedom rates ranging from 41 to 93 % [1, 2]. In patients who have been operated on and who have reached seizure freedom the ultimate goal is to discontinue antiepileptic drug (AED) use and to improve developmental capacities [3–5]. AEDs are known to have cognitive side-effects, particularly in children. Most affected cognitive functions are attention, vigilance and psychomotor speed [6–9]. AED reduction has been reported to improve cognitive processing under time pressure [8, 10], psychomotor speed and alertness [11–13], processing speed [14], verbal memory [15] and Intelligence Quotient (IQ) [9]. The growing body of evidence that cognitive functioning improves after AED withdrawal has increased awareness of the possible benefits of the earliest possible withdrawal of AEDs after epilepsy surgery. Two recently published studies [16, 17] showed that early withdrawal of drug treatment unmasks incomplete surgical success and AED dependency sooner, but not at the cost of worse long-term seizure outcome. Thus, early AED withdrawal would discern the few that require further AEDs from the many that can safely stop, without changing the chance of regaining seizure freedom. A pressing question is whether early AED withdrawal improves cognitive outcome measures, as compared to current care with usually later AED withdrawal. To answer that question we designed a pragmatic randomized clinical trial to investigate the benefits and safety of early AED withdrawal after epilepsy surgery in children. We hypothesize that 1) children who discontinue AED’s early have better cognitive scores, behavior and quality of life than those who discontinue late, particularly at 1 year after surgery (when 1 group is without AEDs and the other is still on AEDs), and maybe persisting from then on, and 2) early AED withdrawal is safe and does not cause more recurrences that are unresponsive to restart of medication, than late withdrawal.

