#### Outcome parameters

Cognitive outcome: differences in EpiTrack scores, IQ scores and other continuous outcome measures of neuropsychological assessment will be analyzed using independent samples *t*-tests or other tests depending on distributions. EpiTrack and IQ differences will be assessed cross-sectionally to answer the primary research question. Additionally, longitudinal changes in EpiTrack measures and IQ compared to preoperatively will be assessed between both treatment arms using linear mixed models. We will calculate a number needed to treat, expressed as the number of patients required to taper drugs earlier to achieve one more patient with improvement in attention. Analyses will be considered statistically significant if 95 % confidence intervals for group differences do not include 0, compatible with a 2-sided *p* < 0.05. For chances of eventual seizure freedom and “seizure and AED freedom”; we will calculate a relative risk and a risk difference with 95 % confidence intervals. Chances of eventual seizure freedom and “seizure and AED freedom” will be compared between the groups at 24 months after surgery and at 20 months following start of AED withdrawal; for the early withdrawal arm this will be at 24 months and for the late withdrawal arm at 32 months.

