**Fig. 2 Fig2:**
[figure not shown]
Sequential testing safety profile. The plot is based on a likely sample size of 75 patients per treatment strategy, a 1-sided α = 0.05, an expected seizure recurrence rate ≤ 30 % and a cut-off point for safety, which is a recurrence rate of ≥ 40 %. The red boundary represents the safety margin. The following formulas will be used to plot data in the graph: *Ζ* = −(*F* − *n* × *Pc*) (→*Ζ* = number of observed seizure recurrences – number of expected seizure recurrences), *V* = *n* × *Pc* (1 − *Pc*) (→*V* is the variance of *Z* and stands for the amount of information in *n* patients, with *n* being the number of included patients, *Pc* the expected seizure recurrence risk (i.e., for the selected patient cohort: 0.30) and *F* the number of observed seizure recurrences). The vertical line is the anticipated value for *V* for a sample size of 75 patients

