## Discussion

We present the protocol of a European pragmatic randomized clinical trial, designed to investigate the possible benefits and the safety of early AED withdrawal after epilepsy surgery in children. We hypothesize that early AED withdrawal is safe, in terms of seizure relapse rates and eventual seizure outcomes, and will improve cognitive functioning, behavior and quality of life, compared to late withdrawal. We will investigate these hypotheses by randomly allocating patients to an early withdrawal group that starts withdrawal of medication 4 months after surgery, versus a late withdrawal group, that starts withdrawal of medication after 12 months. Justification of this trial needs to be discussed. The non-experimental evidence obtained so far on safety of AED withdrawal in relation to seizure outcome seems strong and consistent [16, 17]. In analyses that had been elaborately adjusted for confounding, there was a slightly increased recurrence risk for earlier withdrawal, but not for regain of seizure freedom rates and eventual seizure outcome. Moreover, findings on cognitive outcome after AED withdrawal all pointed towards cognitive improvement on several domains [3–15]. Why then do we think that the trial will have important added value? Through randomized allocation the study population will be broader than in the non-experimental studies which only pertained to patients for whom AED withdrawal had already been decided about. Consequently, results will have wider clinical applicability and will apply to all patients who are eligible for withdrawal decision- making. A very important asset will be obtaining baseline comparability of treatment arms for both known and measurable confounders, but also for unknown or unmeasurable confounders. In principle, the non-experimental evidence, although elaborately adjusted for known confounders, does leave residual confounding as an explanation. The trial will allow for full follow-up of all children randomized and for intention-to-treat analysis. Finally, through the above, stronger evidence will contribute to our ultimate goal, implementation of evidence-based practice concerning AED withdrawal. Although previous non-experimental research does seem to indicate benefits of early AED withdrawal, it is especially the remaining uncertainty about residual confounding that leads us to claim that there currently is genuine equipoise about timing of withdrawal and, therefore, that random allocation is ethically justified. This issue will have to be addressed with regard to trial feasibility. Throughout European centers participating in the trial, there are regional preferences concerning AED withdrawal timing, and non-experimental evidence has already led to changes in clinical practice concerning withdrawal timing. It will be vital for successful completion of the trial that participating physicians can and will be convinced that there still is true equipoise, as a sufficient basis for studying randomized AED withdrawal timing to the ultimate benefit of children who have undergone epilepsy surgery.

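### The only stated criterion for "safe" is a recurrence rate below 40% in each arm taken alone, which does not answer the early-versus-late safety objective

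*Protocol article*

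**What the plan says.** **Objective and hypothesis.** The Design part of the Abstract and the Study objectives section list seizure recurrences among the safety outcomes, and the objectives frame them as early versus late. The Discussion hypothesises safety in terms of relapse rates as well as eventual seizure outcome. The Background states a narrower comparative hypothesis: "early AED withdrawal is safe and does not cause more recurrences that are unresponsive to restart of medication, than late withdrawal".

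**Criterion.** Safety monitoring says that "we will assess safety in each arm separately" and then: "The study intervention will be considered safe when seizure recurrences occur in less than" 40% of both arms. It adds that a 40% "rate of seizure relapse will still be accepted" because of the expected cognitive benefit. The reason for the per-arm approach is that at interim time points more early-arm patients are tapering, so "a fair comparison of relapse between both groups is not feasible".

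**Sequential test.** Recurrences are reviewed every 3 months with a 1-sided p < 0.05. The legend of Fig. 2 sets Pc as "the expected seizure recurrence risk (i.e., for the selected patient cohort: 0.30", for 75 patients per strategy. This test too is run within each arm.

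**Between-arm analysis.** For eventual seizure freedom and seizure-and-drug freedom, Outcome parameters says "we will calculate a relative risk and a risk difference" with 95% intervals. The time points are 24 months after surgery and 20 months after the start of withdrawal (24 months after surgery in the early arm, 32 in the late arm). Recurrence is not in that list.

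**The concern.** A criterion that looks at each arm alone cannot show whether early withdrawal carries more recurrences than late withdrawal. Two arms can both fall below 40% and still differ by a large and statistically clear amount. The sentence is worded as a conclusion about the intervention, and the article gives no other criterion for calling it safe.

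The planned seizure-freedom comparisons do not fill the gap. Patients may restart medication after a recurrence (Study design) and become seizure free again, so an excess of recurrences need not show in eventual seizure freedom. An excess is also a possibility that the article itself raises: the Discussion says that in earlier adjusted analyses "there was a slightly increased recurrence risk for earlier withdrawal".

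At stake is a safety statement about children that sits beside an unreported or unweighed excess of relapses.

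**Working it through.** **Inputs.** 75 per arm (Sample size calculation; Fig. 2); limit 40% and 1-sided 0.05 (Safety monitoring); expected rate 0.30 (Fig. 2); HR 0.94 (0.86 to 1.02) per 3 months' longer interval to start of reduction (Safety monitoring); taper starts 4 and 12 months after surgery, a gap of 8 months (Study design).

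**1. The plan's own figure.** n per arm = 2 × 4.70² × (1.960 + 0.842)² / 2.16² = 74.3, so 75 (the t-based calculation also gives 75, power 0.80). The stated size reproduces, but it is set by the EpiTrack Junior score and not by safety.

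**2. What passes.** 40% of 75 is 30, so the largest passing count is 29 (38.7%).

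| Early | Late | Ratio | Difference (95% CI, Newcombe) | Fisher p | Criterion |
|---|---|---|---|---|---|
| 29/75 (38.7%) | 12/75 (16.0%) | 2.42 | +22.7 points (8.4 to 35.8) | 0.003 | met |
| 29/75 | 14/75 (18.7%) | 2.07 | +20.0 points (5.5 to 33.4) | 0.011 | met |
| 29/75 | 22/75 (29.3%) | 1.32 | +9.3 points (−5.8 to 23.9) | 0.30 | met |

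A ratio above 2 needs a late-arm rate below 38.7% / 2 = 19.3%. At a late rate of 30% the largest passing ratio is 38.7 / 30 = 1.29.

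**3. Reliability within one arm.** P(X ≤ 29 | n = 75, p) is 0.96 at p = 0.30, 0.46 at 0.40 and 0.16 at 0.45. These use the final count alone. They leave out the chance that an arm is flagged at an earlier 3-monthly look, which cannot be computed because the boundary plot is not available.

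**4. Does the sequential test catch the example?** Excess over expected = 29 − 75 × 0.30 = 6.5. V = 75 × 0.30 × 0.70 = 15.75. 6.5 / √15.75 = 1.638, just below 1.645. This is a fixed-sample approximation, again because the boundary cannot be seen. In any case, an alarm against 30% that stays silent is no evidence on the difference between arms.

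**5. What excess the protocol's own data allow.** Assuming a log-linear effect over the 8-month gap, the early/late HR = 0.94^(−8/3) = 1.18; the interval limits give 1.02^(−8/3) = 0.95 and 0.86^(−8/3) = 1.50. From 30% in the late arm, 1 − 0.70^1.18 = 34% in the early arm, with a range of 29% to 41%.

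**6. Does the reason for not comparing carry over to the end of the trial?** No. It rests on unequal exposure to withdrawal at interim looks. Study design says that the arms can be compared at equal drug-free intervals, and Outcome parameters gives the time point. Safety monitoring itself speaks of the total relapse risk at the end of follow-up.

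**7. Precision of the comparison.** At 30% in both arms, the half-width of the 95% interval for the difference is 1.96 × √(2 × 0.30 × 0.70 / 75) = 14.7 points; with 90 per arm it is 13.4.

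**The case against.** The best reply is that the 40% sentence stands under Safety monitoring, between an explanation of why interim comparison is unfair and a description of 3-monthly board reviews. Read there, it is a monitoring limit, and nothing says that the final report will rest on it. That reading is plausible, and if it is the intended one the fix is mostly wording. But the sentence is not restricted to interim use and is phrased as a conclusion about the intervention.

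A second reply is that the Background hypothesis concerns recurrences that do not respond to restarting medication, and that eventual seizure freedom, which is compared between arms, comes closest to it. This stands: the 29/75 against 12/75 example counts all recurrences and does not by itself refute that hypothesis. The mismatch is with the objectives and the Discussion, which name recurrences and relapse rates.

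A reader might infer more, which the article does not support:

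- *That the rule is expected to pass a doubling of recurrences.* This needs a late-arm rate below about 19%, whereas planning uses 30%, and the article's own HR points to about 34% against 30%.
- *That safety rests on a raw percentage with no test.* A per-arm sequential test accompanies it.
- *That seizure outcomes will be judged safe whenever the interval includes 0.* That significance sentence follows the cognitive analyses, and 0 is not the null value of a relative risk. Nowhere does the article say that a non-significant difference proves safety.

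The article is also condensed, so the absence of a fuller recurrence analysis or of a margin is not the point. The point is a criterion that is stated and does not fit the stated objective.

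**Conclusion.** The concern holds in this form: the one criterion given for calling the intervention safe is non-comparative, the objective is comparative, and the reason offered for the per-arm approach lapses once follow-up is complete. With 75 per arm, the criterion can be met alongside a difference as large and clear as +22.7 points (95% CI 8.4 to 35.8). That is an illustration of what the rule permits, not a forecast. If the late arm runs at the planning rate of 30%, the excess that can pass is about 9 points, a ratio of about 1.3.

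The 0.46 pass probability at a true 40% applies to the final count of 75 and ignores earlier sequential looks. The projection to 34% (29% to 41%) assumes that the retrospective HR is log-linear in time and carries over to the trial population. The mismatch itself depends on none of these figures. It should be corrected before the safety conclusion is drawn.

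**What to change.** 1. In Safety monitoring, state that the 40% figure is a monitoring limit for the data safety board and not the basis of the trial's safety conclusion. Reconcile that section with the Background hypothesis, the Study objectives and Outcome parameters.
2. Add seizure recurrence by 20 months after the scheduled start of taper to the outcomes compared between arms by relative risk and risk difference with 95% intervals, analysed as randomised.
3. Base the final safety statement on that interval together with the comparisons of seizure freedom and seizure-and-drug freedom. Report the largest excess of recurrences that the interval does not exclude, and say that a non-significant difference will not be read as proof of safety.

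A stricter per-arm cut-off is not a good substitute. Requiring the 1-sided 95% upper limit to lie below 40% means at most 22/75, which an arm at the planned 30% would reach only 51% of the time, and it would still be non-comparative.

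**Cost.** Some wording and one more table, from recurrence data and a follow-up point already planned; no extra patients and no change to treatment. The price is a more modest claim: with a half-width of about 15 points at 30% per arm, equal observed rates would support only a statement that an excess above about 15 points is unlikely.
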